**Fig. 2 Fig2:**
[figure not shown]
Flowchart of study process

We hypothesized that physical activity level could influence the long-term prognosis of pain and clinical indices of TMD in addition to sleep duration and quality, and other comorbidities related to psychosocial aspects.

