### Statistical analysis

The obtained data will be analyzed using SPSS Statistics ver. 26.0 software (IBM Co., Armonk, NY, USA). The significance level will be set to 0.05. To compare differences between groups, both parametric and nonparametric tests will be adopted accordingly. Descriptive statistics for clinical variables and comorbidity levels will be presented as mean with standard deviation, and median with lower and upper quartiles. Logistic regression will be used to investigate factors associated with a worse long-term prognosis of TMD in terms of pain and function. All potential confounders, including clinical indices of TMD symptoms measured before treatment, body mass index, blood pressure and pulse rate, scores reflecting psychosocial status, sleep quality, and hematologic indices will be included as independent variables along with actigraphy data such as the amount of energy consumption per day, metabolic equivalent of task, steps count, sleep time, wake after sleep onset, sleep efficiency, sleep fragment index, and movement index. Factors will be added first in order to make adjustments, after which will be discarded consecutively one at a time with the first being the one with the highest *p*-value. The cutoff point of confounders to be discarded will be set as *p* < 0.250. If the *p*-value is 0.250 ≤ *p* ≤ 0.300, the confounder will not be discarded if this affects the OR by more than 10% [40]. Receiver operating characteristic (ROC) curves will be analyzed to explore thresholds for potential biomarkers. Their prognostic values will also be assessed by using Kaplan–Meier curve and both univariate and multivariate COX regression models. If the estimated sample size is not reached, multiple imputation will be used for missing data. A single overall analysis result will be produced by combining multiple analysis results.

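### The elimination rule protects no term, so the activity odds ratio adjusted for sleep and psychosocial factors that the hypothesis calls for is not guaranteed

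*Protocol article*

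**What the plan says.** The hypothesis stands at the end of the Study outcomes section, below Fig. 2: "physical activity level could influence the long-term prognosis of pain and clinical indices of TMD in addition to sleep duration and quality", followed by other psychosocial comorbidities. The Background adds that the influence of sleep needs to be controlled.

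The Statistical analysis section describes the model meant to address prognosis: "Logistic regression will be used to investigate factors associated with a worse long-term prognosis of TMD in terms of pain and function". The potential confounders, among them "scores reflecting psychosocial status, sleep quality, and hematologic indices will be included as independent variables along with actigraphy data", enter together with a list of actigraphy indices: daily energy consumption, "metabolic equivalent of task, steps count, sleep time, wake after sleep onset, sleep efficiency, sleep fragment index, and movement index". That is eight indices, of which at least three (energy consumption, metabolic equivalent, steps) measure activity and several measure sleep. None is named as the main exposure.

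Selection follows: "Factors will be added first in order to make adjustments, after which will be discarded consecutively one at a time", starting with the highest p-value. The cut-off is 0.250. For p between 0.250 and 0.300 there is one exception: "the confounder will not be discarded if this affects the OR by more than 10" per cent.

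**The concern.** An effect of activity in addition to sleep and psychosocial status is a conditional effect. It is estimated by an activity coefficient in a model that also holds the sleep and psychosocial terms. A rule that can remove any of these terms according to the data does not secure that coefficient.

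Three things are at stake:

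- If the activity terms are removed, the final model has no activity odds ratio. A weak or null effect is then left out rather than reported with a confidence interval.
- If a sleep or psychosocial term is removed, the remaining activity odds ratio is no longer adjusted for what the hypothesis names.
- If activity stays because its p-value was small enough, its estimate has been selected for size, and the usual confidence interval ignores that selection.

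The concern does not depend on how many candidates are listed, nor on the direction of the printed cut-off. That cut-off read literally discards small p-values and conflicts with removing the highest first. The check below takes the evident intention, removal when p exceeds 0.25.

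**Working it through.** **Step 1. Which terms are protected?**

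| Term | Role in the hypothesis | Status under the elimination rule |
|---|---|---|
| Sleep quality, psychosocial scores | must be adjusted for | listed as confounders; removable |
| Actigraphy sleep time and related indices | must be adjusted for | entered with the actigraphy data; no protection stated |
| Activity indices (at least three) | exposure under test | removable if *Factors* means all entered terms; unclear otherwise |
| Odds ratio in the 10% rule | should be the activity odds ratio | not identified among several indices |

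The 10% exception applies only to p from 0.250 to 0.300, so it gives no protection above 0.300.

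**Step 2. Inputs for the size.** The Sample size calculation gives 214 participants and 20% dropout: 214 × 0.8 = 171. The article gives no proportion with poor prognosis, no correlations and no effect sizes. Assumed: 30% events; 10 normal predictors with pairwise correlation 0.3; true OR per SD of 1.3 for a sleep term, 1.3 for a psychosocial term and 2.0 for baseline severity; the stated OR for activity; zero for the rest.

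**Step 3. Hand approximation for one activity term.**

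- R² on the other nine predictors = 9 × 0.3² / (1 + 8 × 0.3) = 0.81 / 3.4 = 0.238. Variance inflation = 1 / (1 − 0.238) = 1.313.
- SE of the log OR ≈ √[1.313 / (171 × 0.3 × 0.7)] = √(1.313 / 35.91) = 0.191.
- A term stays if |estimate / SE| exceeds c = z(0.875) = 1.150.
- P(deleted) = Φ(c − δ) − Φ(−c − δ), with δ = ln(OR) / 0.191.

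| True OR per SD | δ | P(deleted) |
|---|---|---|
| 1.0 | 0 | 75% |
| 1.2 | 0.95 | 56% |
| 1.3 | 1.37 | 41% |
| 1.5 | 2.12 | 17% |

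The same threshold shows the inflation. To survive, the estimate must be at least exp(1.150 × 0.191) ≈ 1.25 or at most about 0.80. A true OR of 1.2 therefore cannot be reported as about 1.2, because an estimate that size is removed.

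**Step 4. Simulation of the whole backward procedure** (same assumptions, 1,500 runs per setting, rounded over independent repeats).

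| True OR per SD | One activity term: deleted | Three activity indices (assumed correlation 0.8): all deleted |
|---|---|---|
| 1.0 | about 70% | about 36% |
| 1.2 | about 55% | about 29% |
| 1.3 | about 43% | about 21% |
| 1.5 | about 20% | about 8% |

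A sleep term with true OR 1.3 is deleted in about 42% of studies. In the one-term design, at least one of the activity, sleep and psychosocial terms is missing from the final model in 77–91% of runs.

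For a single activity term that is retained:

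- At true OR 1.2, the median reported OR is about 1.46 and the 95% CI covers the truth in 85–87% of runs. Without elimination, such data give a median of 1.22 and 95% coverage, so the distortion comes from the selection.
- Coverage is 75–80% at OR 1.0, about 92–93% at OR 1.3 and about 95% at OR 1.5.

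**Step 5. A longer candidate list.** With 23 terms (three activity indices, four sleep, four psychosocial, 12 others; 171 patients; 300 runs per setting; cut-off 0.25), all activity indices are removed in 36% / 28% / 11% / 1% of runs at OR 1.0 / 1.2 / 1.4 / 1.7. At least one whole domain is lost in 49% / 46% / 35% / 24%.

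**The case against.** The best defence is textual. The confounders and the actigraphy data are named as two classes, and the cut-off and the 10% exception speak only of confounders and of a single odds ratio. On that reading actigraphy is the exposure, stays in, and is the yardstick for change in estimate. This is a fair reading, so deletion of activity is a risk from unclear wording and not a settled rule. It still does not say which of several indices supplies the odds ratio, and it leaves the sleep-quality and psychosocial terms removable.

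A reader might go further and infer that the study could end with no estimate for its own hypothesis. The article does not support that. Elimination starts from a full model containing all three domains, and the section also plans group comparisons, ROC curves, and univariate and multivariate Cox models with no stated elimination rule. Any of these may yield an activity result. However, the group tests are unadjusted, the Cox covariates are not listed, and reporting of the starting model is not promised. Dropping a sleep or psychosocial term also leaves an activity odds ratio, only a less adjusted one.

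Two points on size also stand. The one-term deletion rates are too high for a model with several activity indices, which is why both versions are shown. Undercoverage is serious only for null to weak effects. Finally, the hypothesis does not demand a formal nested comparison; an adjusted odds ratio from one fixed model answers it.

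This is not a detail left to an analysis plan: the article itself prescribes the procedure and its cut-offs.

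**Conclusion.** The point holds in limited form. As written, the rule does not guarantee the activity odds ratio adjusted for sleep and psychosocial factors. Removal of those adjusters follows from the stated rule; removal of activity follows on its plain reading. The odds ratio in the 10% rule has no named exposure.

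For a weak effect (true OR 1.2 per SD), activity vanishes from the final model in about 29% of studies with three correlated indices and about 55% with one. At OR 1.5 the figures are about 8% and 20%. Inflation and undercoverage matter for null or weak effects and largely fade by OR 1.5 for a single term. These rates rest on the assumed event rate, correlations and effect sizes, none of which the article gives. The textual conflict does not depend on them. The change should be made; the study is not invalid without it.

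**What to change.** In the Statistical analysis section:

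1. Name one main activity measure, for example the MVPA measure from the Patient grouping section.
2. Keep in the model, whatever their p-values, that measure, the baseline value of the outcome, and pre-specified sleep and psychosocial covariates.
3. Report the activity odds ratio with its 95% CI whether or not it is significant.
4. Apply elimination and the 10% rule only to the remaining covariates, and state that the 10% change is judged on that activity odds ratio.

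A likelihood-ratio test for adding activity and the change in AUC are optional extras.

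The cost is wording only, with no new data. The downside is that a few non-significant terms stay in the model. With activity and the core covariates held in, the chance that the rule removes them is zero, and no stated figure in the article changes.

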### Sample size calculation

Sample size estimation for this study was based on the primary outcome of physical activity level measured in minutes and 77.8 min as between-group difference. A total of 214 participants (107 per group) will be needed based on analysis to reach the power of 90% with an alpha error of 0.05 and an estimated study dropout rate of 20%.

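### The backward-elimination rule contradicts itself: its discard cut-off is written as p < 0.250, against the sentences before and after it, and nothing is stated for p > 0.300

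*Protocol article*

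**What the plan says.** All of this is in the protocol article, under Statistical analysis. The model is introduced with: "Logistic regression will be used to investigate factors associated with a worse long-term prognosis of TMD in terms of pain and function". Potential confounders and a list of actigraphy measures enter together. Three consecutive statements then govern removal.

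1. Order: factors are "discarded consecutively one at a time with the first being the one with the highest *p*-value".
2. Cut-off: "The cutoff point of confounders to be discarded will be set as *p* < 0.250".
3. Exception: "If the *p*-value is 0.250 ≤ *p* ≤ 0.300, the confounder will not be discarded if this affects the OR by more than 10" percent.

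The third statement cites a source for the approach. That source is not at hand, so the intended rule cannot be checked against it.

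**The concern.** Statement 2 attaches discarding to small p-values, and statements 1 and 3 attach it to large ones. They cannot all be followed. There is also no explicit instruction for p > 0.300, where most irrelevant covariates will fall.

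The study is observational, and the Background of the article names psychological status and sleep quality as confounders to be taken into account. Covariate adjustment is therefore an important protection for any association between activity and prognosis. As worded, the rule allows more than one final model from the same data, so the choice between them could be made after the results are seen. An analyst who programs statement 2 as it stands would remove the covariates that most need to stay.

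**Working it through.** **Side by side.** The cut-off is a rule, not a calculated figure, so there is nothing to reproduce. The check is whether the three statements can hold together.

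| p-value | Cut-off sentence read alone | Read with the sentences on either side |
|---|---|---|
| below 0.250 | discard | keep |
| 0.250 to 0.300 | not in the discard range, so the exception has nothing to except | discard, unless the OR changes by more than 10% |
| above 0.300 | no instruction | discard (implied, not stated) |

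The exception decides the matter. A reprieve just above 0.250 is meaningful only if factors there would otherwise be discarded. That makes p < 0.250 the criterion for retention. Removing the highest p-value first points the same way.

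**Illustration of the two readings (assumed inputs).** The number analysed is 214 × (1 − 0.20) = 171.2, about 171, using the total and dropout rate in Sample size calculation. Everything else is assumed: 1,000 simulated data sets; an exposure with true OR 1.0 that always stays in the model; three true confounders, each with log-OR 0.7 and correlation 0.4 with the exposure; seven noise covariates; and the outcome present in about half of participants. The literal version may discard only covariates with p < 0.250. The contextual version discards at p > 0.300, discards at 0.250 to 0.300 unless the exposure OR changes by more than 10%, and keeps p < 0.250.

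| Procedure | True confounders kept | Noise covariates kept | Mean exposure OR (truth 1.0) |
|---|---|---|---|
| Full model, no elimination | 100% | 100% | 1.00 |
| Contextual rule | 99% | 26% | 1.00 |
| Cut-off read literally | 0.8% | 63% | 2.13 |

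**How the size varies.** A simpler comparison has one confounder either in or out of the model, with n = 171, about 30% worse prognosis, a null activity effect and correlation −0.4 with activity. It does not run the elimination sequence; it shows only what omission would cost.

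- Confounder log-OR 0.7 per SD: it has p < 0.250 in 99.6% of samples. Leaving it out moves the activity OR from 1.01 to 0.77 and the false-positive rate from 4.1% to 32.8%.
- Confounder log-OR 0.3 per SD: leaving it out gives an OR of 0.89 and a false-positive rate of 8.6%.

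The bias is above 1 in the first illustration and below 1 here because the assumed correlation with the exposure has the opposite sign.

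**A third reading.** Suppose the literal cut-off is combined with highest-p-first, and the procedure stops at the first factor that fails the discard condition. Nothing is then removed unless every candidate has p < 0.250. For seven independent noise covariates alone, that has probability 0.25^7 = 0.00006. The full model stays, with a mean OR of 1.00.

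**The case against.** The best reply is that this is a slip that any statistician would correct on reading. The sentences on either side show that p < 0.250 is meant to be kept, and under that reading the simulated OR is unbiased. This largely stands, and it limits the consequence. It does not remove the fault: a prespecified rule should not depend on the reader reversing its inequality. Nor is this a detail left to an analysis plan that is not shown, because the article states the rule and states it inconsistently.

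Some stronger readings are tempting, and the article does not support them.

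- A reader might infer that the model will drop the strongest confounders and keep the noise. That follows only if the cut-off sentence is isolated from its neighbours. Even a literal reading can leave the full model untouched, as the third reading shows.
- A reader might take the simulated ORs and false-positive rates as the expected bias of this study. They rest on assumed event rates, effect sizes and correlations that the article does not give.
- A reader might treat this model as the main adjusted estimate. The article does not call it that. It stands beside group comparisons, ROC curves, Kaplan–Meier curves and Cox models, and the sample size rests on a between-group difference in activity minutes.
- A reader might also call it an error that the 10% check stops at p = 0.300. That is a design choice. With correlation −0.4 between confounder and activity, 0 to 0.2% of simulated samples had both p > 0.300 and an OR shift above 10%. The share reached 7.5% to 15% only at correlations of −0.6 to −0.7, with confounder log-OR 0.2 to 0.3.

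**Conclusion.** The elimination rule is self-contradictory as written and has no stated instruction for p > 0.300. This rests on the text alone and needs no assumption. The reversed inequality is most probably a drafting error, judged from the adjoining sentences and without sight of the cited source.

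The consequence is conditional. If the cut-off were applied literally, the confounders most related to prognosis would be the ones removed, and the activity odds ratios could be biased. On the assumed inputs, a null effect appeared as an OR anywhere from 0.77 to 2.13, depending on the number, strength and sign of the confounders. If the evident intent is followed, no such bias arises from this source. The point should be fixed, but it is not one on which the analysis stands or falls.

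**What to change.** Replace the cut-off and exception sentences with one rule that covers every p-value:

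- p < 0.250: the confounder is retained.
- 0.250 ≤ p ≤ 0.300: it is discarded unless its removal changes the OR of the named activity exposure by more than 10%.
- p > 0.300: it is discarded.

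The exposure has to be named because the article enters several activity measures (energy consumption, metabolic equivalents, step count, movement index), so reference to the OR alone does not identify one.

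Two additions are optional: applying the 10% check above 0.300 as well, and keeping a fixed set of covariates whatever their p-value. Both would leave more terms in a model that already has many candidates.

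The cost of the correction is one or two sentences. It needs no new data.

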## Background

Temporomandibular disorders (TMD) is a disease usually represented by discomfort and/or dysfunction of the masticatory muscles and temporomandibular joints (TMJ) leading to impairment of basic daily functions such as chewing and speaking. It is known as the most prevalent cause of nonodontogenic pain in the orofacial region, which 5–12% of the adult population experience [1]. Many factors have been identified to cause and exacerbate its symptoms including sleep quantity and quality, genetic, hormonal, anatomical, and psychosocial factors [2, 3].

Physical activity has been known to affect symptoms in various pain disorders. Exercise is significantly associated with lower perceived pain levels in fibromyalgia patients, while high-intensity exercise was reported to increase pain levels in fibromyalgia patients [4]. Low back pain is also known to be aggravated by higher activity levels [5]. The underlying mechanisms of such interactions are not fully understood. The increase in inflammatory mediators with high-intensity exercise may directly cause an increase in pain levels [6]. However, another previous study reported lower inflammatory biomarker levels including high sensitivity C-reactive protein (hsCRP) with moderate to vigorous physical activity [7], suggesting a complicated interaction between the two. Contradictory results can also be found in clinical reports regarding pain disorders, which involve regular physical activity [8, 9]. Such inconsistencies are largely due to the heterogeneity of the studies in defining physical activity levels and patient groups.

In spite of its profound impact on quality of life and high prevalence, no previous study has prospectively investigated the correlation between TMD and physical activity while considering well-known confounders such as psychological status and sleep quality in addition to hematological markers of systemic inflammation. Since the quantity and quality of sleep can significantly affect pain, it is also necessary to control its influences. Physical activity, sleep duration, and TMD pain are strongly interrelated as they affect one another through overlapping mechanisms.

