## Objectives

Therefore, the main objectives of this “Physical Activity in TMD (PAT)” study are,To assess the long-term effect of objective physical activity level and sleep duration on clinical characteristics in well-defined TMD patient groups.To analyze the impact of physical activity on treatment response to conventional TMD management approaches by determining the cut-off value for physical activity that affects treatment prognosis.To define the causal relationship between abnormal physical activity levels and sleep durations on chronic, high-intensity TMD pain, its comorbidities, and systemic inflammatory marker levels.

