## Methods and design

### Participants, interventions, and outcomes

#### Study design

This is a longitudinal cohort study being conducted prospectively in Seoul National University Dental Hospital from May 2021. It was approved by the Institutional Review Board (IRB) of the same hospital (#CRI21007). The study is registered in Clinical Research Information Service, an online registration system for clinical researches (registration number KCT0007107). The system includes all items from the trial registration data set of the World Health Organization (version 1.3.1). Written informed consent is collected from all participants by YC. Further modifications to the study protocol that occur after IRB approval will be reported to the review board and relevant parties for additional permission. In case of any major modification of protocol version 1.0, the issue will be thoroughly discussed with the IRB. Whenever there is a change, a new protocol version will be assigned. All procedures complied with multiple ethical standards of the institutional research committee, the Helsinki declaration in 1964, and its later amendments or other equivalent ethical standards.

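### If ROC-derived thresholds define the Kaplan–Meier and Cox groups in the same cohort, as the text most naturally reads, the resulting p-values are not valid at 0.05

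*Protocol article*

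**What the plan says.** All references are to the protocol article.

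- **Statistical analysis** sets one level for everything: "The significance level will be set to 0.05". Two consecutive sentences then read "Receiver operating characteristic (ROC) curves will be analyzed to explore thresholds for potential biomarkers" and "Their prognostic values will also be assessed by using Kaplan–Meier curve and both univariate and multivariate COX regression models".
- **Objectives**: the second of the three main aims, on treatment response, is to be met "by determining the cut-off value for physical activity that affects treatment prognosis". ROC is the only method named anywhere for finding a threshold.
- **Study design**: there is one single-centre cohort, "This is a longitudinal cohort study being conducted prospectively in Seoul National University Dental Hospital from May 2021". No second cohort, split sample, resampling or selection-corrected p-value is described.
- **Patient grouping** separately fixes an Active/Inactive split (150 minutes of moderate or 75 minutes of vigorous activity per week) and a low/high disability split on the GCPS. Neither is derived by ROC.

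**The concern.** An ROC threshold is placed where it best separates patients with good and poor outcomes. If the two resulting groups are then compared on that outcome in the same patients, the comparison has been tilted before it is made. A log-rank or Cox p-value treats the groups as if they had been fixed beforehand, so it is too small. The sensitivity, specificity and hazard ratio attached to the chosen cut-off are too favourable for the same reason.

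This touches a main objective. The Discussion also expects the study's data to support guidance on physical activity and the diagnostic value of the measurements. An activity cut-off that appears prognostic through selection alone would weaken that contribution.

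**Working it through.** **1. Inputs from the article.** Level 0.05, with sidedness not stated and taken here as two-sided. Visits at baseline, 6 and 12 months. For size, Sample size calculation says "A total of 214 participants (107 per group) will be needed based on analysis to reach the power of 90" per cent, with 20% dropout.

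**2. The plan's own figure.** The 214 cannot be reproduced, because the SD is not given with the 77.8-minute difference. Solving backwards from n per group = 2(1.960 + 1.282)² SD² / 77.8², with 85 evaluable per group (85/0.8 = 106.25, rounded up to 107), gives SD ≈ 156 minutes, or a standardised difference of about 0.50. Only N matters below: 214 with no loss, or 214 × 0.8 ≈ 171 after dropout.

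**3. Assumptions not in the article.**
- 12-month share with poor outcome: 20%, 30% or 50%.
- Selection rule: largest Youden index, J(c) = sensitivity + specificity − 1.
- Direction: either free (the larger |J| in either direction) or fixed in advance.
- Cut-off search: over all values, the central 80% or the central 50%.
- The ROC and the Kaplan–Meier/Cox analysis use the same outcome.

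**4. Simulation with no true effect.** There were 10,000 runs per setting. A continuous marker is drawn independently of outcome. Events are recorded at the 6- or 12-month visit, with hazard λ = −ln(1 − p)/12 per month. The cut-off maximises J. The two groups are then compared in the same patients by the log-rank statistic (O − E)²/V against 3.84, which is the score test of a univariate Cox model. The Monte Carlo standard error is at most √(0.4 × 0.6 / 10,000) ≈ 0.5 percentage points.

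Share of runs with p < 0.05 (ranges over both N and all event shares):

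| Cut-off search | Direction free | Direction fixed |
|---|---|---|
| All values | 39–41% | 23–24% |
| Central 80% | 36–39% | 19–21% |
| Central 50% | 27–28% | 13–15% |

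The ratios to nominal run from 13/5 = 2.6 to 41/5 = 8.2. Neither N nor the event share moves the results much.

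**5. Comparators, which isolate the cause.**
- Cut-off fixed beforehand at the median: 4.7–5.3%.
- Cut-off found in one half and tested in the other: 4.6–5.6%.
- Marker kept continuous (N = 171, 30% events): about 4.7%.
- Cut-off chosen on an unrelated outcome (N = 171, 30% events): 4.8–4.9%.

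The inflation therefore comes from selecting and testing on the same outcome in the same patients.

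**6. Two further measures of size.** To hold a true 5% after same-sample selection, the nominal p would have to be about 0.003–0.004 (N = 171, 30% events). In a separate simulation with direction free (N = 171, 20–40% poor outcome), the apparent Youden index was 0.13–0.16, where the true value is 0. That is the optimism in sensitivity plus specificity.

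The multivariable Cox model was not simulated. Adjusting for covariates does not undo selection of the cut-off. Searching several actigraphy and blood markers would add multiplicity that is not counted here.

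**The case against.** **The text does not say that ROC groups enter the survival models.** *Their* may refer to the biomarkers rather than the thresholds, and *also* may signal a parallel analysis. A Cox model on a continuous marker holds its level. This stands, and it is why the point is conditional. However, Kaplan–Meier curves need groups, and the sentence just before supplies thresholds. The wording at least permits the invalid test.

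**Pre-set groups exist.** The curves could be drawn on the splits in Patient grouping, with no inflation. This also stands for those analyses. But the 150/75-minute split is given in advance, so it cannot be the cut-off that the second objective sets out to determine.

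**The ROC sentence speaks of biomarkers.** Secondary outcomes applies that word to blood-count ratios, so linking the sentence to activity is an inference. It is a reasonable one, since no other route to the activity cut-off is named.

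**The step is exploratory, and another test is planned.** The ROC sentence does say *explore*. The logistic regression takes actigraphy measures as independent variables with no mention of dichotomising them, so an association test free of the cut-off is available. Resampling detail may also sit in a fuller document. All of this limits the damage. The point, though, concerns a stated sequence rather than an omitted detail.

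**Stronger readings that the article does not support.**
- *That a U-shaped relation would be missed.* A reader might infer this from Background, where "high-intensity exercise was reported to increase pain levels in fibromyalgia patients". That evidence comes from fibromyalgia, and the adverse effect of activity from low back pain; both are exclusions under Participants and eligibility criteria. The functional form of the regressions is not stated either.
- *That the guideline would rest on this cut-off.* The Discussion refers to the study's data as a whole.
- *That the cut-off would fail to reproduce.* Simulations with no true effect show how often a worthless marker passes. They do not show whether activity is worthless here.

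**Conclusion.** The concern holds in conditional form. If ROC-derived groups enter the Kaplan–Meier and Cox analyses, as the two sentences most naturally read, the resulting p-values are not valid at 0.05, and sensitivity, specificity and hazard ratio are optimistic. A marker with no prognostic value would pass about 13–41% of the time, roughly 3 to 8 times nominal. This rests on Youden selection, 20–50% poor outcome, 171–214 patients and a common outcome for both steps. The top of the range needs direction left free and little or no trimming, neither of which the article states, so about 40% should not be quoted as the expected rate. Analyses on the pre-set 150/75-minute groups, or on a continuous marker, keep their level. The flaw affects a main objective but can be repaired entirely at the analysis stage, so it should be corrected.

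**What to change.** - Base the p-value for physical activity on the continuous measure, with a check for non-linearity, or on the pre-set Active/Inactive groups.
- State which groups the Kaplan–Meier curves and Cox models use.
- Report any ROC cut-off as exploratory. Bootstrap the whole selection, repeating the search in each resample, and give optimism-corrected sensitivity and specificity and a confidence interval for the cut-off.
- Do not report uncorrected log-rank or Cox p-values for ROC-chosen groups.

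No new data are needed. The cost is a little extra analysis and a cut-off that will look less impressive.
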